### Analysis and reporting

All randomised patients will be included in the analysis, following the intention-to-treat principle. The comparison of the primary end point will be performed on a per-protocol population, which excludes participants who are mistakenly randomised (in violation of the inclusion and exclusion criteria) and those who withdraw or are lost to follow-up prior to reaching the primary end point.

The primary end point will be compared between the study arms on the basis of a lognormal accelerated failure time regression model, which models the log-transformed outcome as depending linearly on covariates plus a normally distributed error term for unexplained variation [27]. It generalises the standard linear regression model of the log-transformed outcome to right-censored or interval-censored outcome data that are required for analysing our primary end point. If parents or guardians cannot specify the exact time of cessation of diarrhoea, then the assessment by the nurse on duty who assesses the child every 12 hours will be used instead (treated as an interval-censored outcome).

Children who are withdrawn or lost to follow-up before the cessation of diarrhoea will be treated as censored on the day of withdrawal or loss. The primary analysis will not adjust for any covariates, but, in a second step, we will additionally explore the effect of the following covariates on the duration of diarrhoea: duration of diarrhoea prior to enrolment, prior treatment with antibiotics and prior treatment with probiotics, age and diagnosed pathogen by culture or PCR. Likewise, homogeneity of the treatment effect will be assessed according to the subgroups defined by these. The secondary end point of the time from the first dose of study medication to the start of the first 24-hour diarrhoea-free period as assessed by the parents or guardians will be analysed in the same way as the primary end point. Other secondary end points will be compared between the treatment arms on the basis of logistic regression for binary data, Poisson regression for count data, linear regression for continuous data and the lognormal accelerated failure time model for time-to-event data. The comparison of viral load outcomes for norovirus and rotavirus detected by RT-PCR will be adjusted for the participant’s baseline viral load to increase power.

The results of this trial will be reported in one or several peer-reviewed publications.

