### Primary end point

The primary end point is the time from the first dose of study medication to the start of the first 24-hour period without diarrhoea as assessed by the nurse on duty.

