### Sample size and statistical considerations

Data originating from three hospitals in Ho Chi Minh City suggest that the median duration of hospitalisation in our target population is 5 days (interquartile range = 3 to 6 days; mean and standard deviation [SD] of log_10_ duration = 0.61 and 0.27, respectively) and an approximately normal distribution of the log-transformed data. As we have limited preexisting data on the overall length of diarrhoeal illness (prehospitalised and hospitalised), and as children are usually discharged at the time of resolution of diarrhoea, we used the variability of the length of hospitalisation as the basis of our sample size calculation using R software version 2.15.1. This study is designed to test the hypothesis that probiotic therapy is superior to placebo for the treatment of acute watery diarrhoea. It is powered to detect a 20% decrease in the duration of acute watery diarrhoea (corresponding to an absolute effect size of approximately 24 hours) of twice the standard dose of probiotics compared to placebo. For 80% power with a two-sided 5% significance level, a total of 123 participants per study group are required. To account for potential inadequacies in our assumptions and some loss to follow-up, the sample size was increased by 22%. Therefore, a total sample size of 300 participants (150 in each group) will be recruited.

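### The protocol contradicts itself on the primary analysis set: read literally, the primary superiority comparison drops children who leave before the end point, whom the same section also says to censor

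*Protocol article*

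**What the plan says.** All the relevant rules stand in the protocol article under Analysis and reporting.

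- Rule 1, overall principle: "All randomised patients will be included in the analysis, following the intention-to-treat principle".
- Rule 2, set for the primary comparison: "The comparison of the primary end point will be performed on a per-protocol population, which excludes participants who are mistakenly randomised". The sentence goes on to exclude also "those who withdraw or are lost to follow-up prior to reaching the primary end point".
- Rule 3, handling of children who leave while diarrhoea persists: they "will be treated as censored on the day of withdrawal or loss".

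The same section selects a lognormal accelerated failure time (AFT) model because it extends to "right-censored or interval-censored outcome data that are required for analysing our primary end point". The hypothesis is one of superiority, stated under Sample size and statistical considerations: "This study is designed to test the hypothesis that probiotic therapy is superior to placebo for the treatment of acute watery diarrhoea".

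**The concern.** Rules 2 and 3 concern the same children and the same end point but give opposite instructions. Rule 2 also departs from rule 1, and nothing in the text ranks the three.

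The literal reading is the less favourable one. Rule 2 speaks of the comparison of the primary end point without any word such as additional or supportive, and no sentence assigns that end point to the intention-to-treat set. The exclusion of leavers then depends on what happens after randomisation and is related to the outcome, because a child with longer diarrhoea has more time in which to leave. Dropping leavers therefore tends to remove long durations. If the arms lose children at different rates, the distortion differs between them and the duration ratio shifts. It also discards the partial follow-up of these children, which the chosen model could use.

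With two incompatible sets in the published protocol, the choice between them could also be made after the data are seen. Excluding mistakenly randomised children conflicts with rule 1 as well, but it rests on entry criteria and is the lesser problem.

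**Working it through.** **The plan's own figure.** Inputs from Sample size and statistical considerations: SD of log10 duration 0.27, a 20% decrease (ratio 0.80), two-sided 5%, 80% power.

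- Difference on the log10 scale: −log10(0.80) = 0.0969.
- n per arm = 2 × (1.96 + 0.8416)² × 0.27² / 0.0969² ≈ 122 by the normal approximation. The t-test version gives 122.8, so 123, as stated.
- 123 × 1.22 = 150.06, so 150 per arm, as stated.
- Power with every duration observed: 87.5% at 150 per arm and 80.4% at 123 per arm. The inflation thus covers a loss of 1 − 123/150 = 18%. The main issue is bias rather than sample size.

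**Effect of excluding leavers, observation to day 5.** Durations are lognormal with log10 mean 0.61 and SD 0.27 (from the protocol), with 150 per arm. Withdrawal times are exponential and independent of duration. The hazards are assumptions, since the protocol gives none. The ratio is active over placebo.

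| Assumed withdrawal per day (placebo / active) | True ratio | Leavers excluded | Leavers censored |
|---|---|---|---|
| 8% / 2% (about 26% / 7% leave, 16% overall) | 1.00 | ratio about 1.05, rejection roughly 8–10% | ratio 1.00, rejection about 4–6% |
| 8% / 2% | 0.80 | ratio about 0.84, power 53–60% | power about 80% |
| 2% / 8% | 1.00 | ratio about 0.95, rejection about 10% | – |
| 2% / 8% | 0.80 | ratio about 0.76 (exaggerated) | – |
| 3% / 2% | 1.00 | ratio 1.01, rejection 4.8% (500 trials) | – |
| 5% / 5% | 0.80 | power about 78–79% | power about 79–82% |

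The 8–10% for the first row is the spread over runs of 500 to 3,000 trials: about 8%, 8.6% (Monte Carlo standard error 0.5%) and about 10%.

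**Large-sample check without the day-5 limit** (200,000 per arm; rejection and power scaled to 150 per arm, leavers excluded):

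- Null true, equal loss of 11% or 21%: ratio 1.00, rejection 5%.
- Null true, loss 21% placebo and 6% active: ratio 1.07, rejection 13.5%. Reversed: 0.94 and 13%. Loss 36% and 11%: 1.12 and 30%.
- True ratio 0.80, equal hazards: 0.81. Loss 21% placebo and 5% active: 0.855, power 55%. Loss 6% and 17%: 0.76.
- Censoring the same children returned 1.00 or 0.80 in every case, within simulation error.

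**When withdrawal depends on duration.** With a hazard that rises with the child's underlying duration (assumed base 6% placebo, 1.5% active), censoring itself gave a null ratio of 1.06 with 11% rejection. Exclusion gave 1.13 with 32%. Censoring remains better, but it is no longer unbiased.

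**The case against.** The strongest reply is that the article may have condensed two analyses: an intention-to-treat analysis to which the censoring rule belongs, and a per-protocol analysis to which the exclusions belong. All three rules could then stand. This is possible, but the text does not say it, and if it was meant the sentence still needs correcting so that the primary set is named.

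The second reply is that the harm is conditional, and this stands. The trial is double-blind and placebo-controlled, the protocol describes probiotics as well tolerated, and children stay in hospital until 24 hours after symptoms cease or the 5-day course ends. None of this rules out unequal loss, but nothing in the documents supports a fourfold gap in withdrawal either. With a small gap the type I error is indistinguishable from nominal.

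Two stronger readings are tempting and not supported:

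- A reader might infer that the exclusion keeps only children who reached the end point. It does not: a child still ill at day 5 who has neither withdrawn nor been lost is retained.
- A reader might infer that the exclusion makes the AFT model pointless. It does not: the model is also there for interval-censored times from the 12-hourly nurse assessments.

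**Conclusion.** The contradiction is established by the wording alone and needs no assumption. As written, the set for the primary comparison is wrong for a superiority trial.

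The statistical harm is a risk, and its size and direction depend on loss by arm, which cannot be known in advance. Under the assumed 8% and 2% per day, it amounts to a null ratio of about 1.05 with roughly 8–10% rejection, and to a true 0.80 shown as about 0.84 with power down from about 80% to 53–60%. The reverse pattern would flatter the probiotic. With equal loss there is essentially no bias, and the power cost is a few percentage points at most. A reader might infer that the primary result is bound to be biased; the documents do not support that, since they give no dropout rate and no sign of unequal loss.

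Censoring removes the bias only if withdrawal is non-informative. If families leave because diarrhoea persists, it reduces the problem without removing it. The sample size is not affected.

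**What to change.** In Analysis and reporting:

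1. State that the primary analysis includes all randomised children in their assigned arm, and that those who withdraw or are lost before cessation of diarrhoea are kept and right-censored, as the section already provides.
2. Remove withdrawal or loss before the end point as a reason for exclusion from the primary comparison.
3. Label any per-protocol analysis as supportive.
4. Add that censoring assumes non-informative withdrawal.

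The cost is the rewording of a few sentences. No further patients or data are needed, and 123 per arm inflated to 150 stays as it is. The Trial status section says that recruitment has not started, so the change can be made before any outcome data exist.

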**Methods:**

This RCT was designed to study the effect of treatment with *L. acidophilus* (4 × 10^9^ colony-forming units/day) for 5 days for acute watery diarrhoea against a placebo in 300 children ages 9 to 60 months admitted to hospitals in Vietnam. Clinical and laboratory data plus samples will be collected on admission, daily during hospitalisation, at discharge, and at follow-up visits for a subset of participants. The primary end point will be defined as the time from the first dose of study medication to the start of the first 24-hour period without diarrhoea as assessed by the on-duty nurse. Secondary endpoints include the time to cessation of diarrhoea as recorded by parents or guardians in an hourly checklist, stool frequency over the first 3 days, treatment failure, rotavirus and norovirus viral loads, and adverse events.

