### Secondary end points

The following are the secondary end points:

1. The time from the first dose of study medication to the start of first 24-hour diarrhoea-free period as recorded by parents or guardians in an hourly checklist, which will be collected by the nurses on duty every 12 hours.

2. Treatment failure, defined as the occurrence of (a) No resolution of diarrhoea after 5 days of treatment, (b) severe symptoms for which treatment is stopped, such as the development of severe dehydration, renal failure, (septic) shock, respiratory distress or other syndromes associated with diarrhoeal disease as complications (e.g., pneumonia) [5]; and (c) additional antiemetic (domperidone) or antidiarrhoeal (aluminium silicate or racecadotril) treatment.

3. The frequency of stools during the first 3 days after the first dose of study medication.

4. The load in copies per millilitre of viral transport medium of norovirus and rotavirus measured by RT-PCR, assessed daily from admission until discharge and at follow-up.

5. The duration of hospitalisation, defined as the number of days from hospital admission until discharge.

6. The extent of intestinal *L. acidophilus* colonisation, assessed by analyses of faecal samples or rectal swabs collected on admission, on discharge and at outpatient follow-up for the first 50 participants who agree to participate.

7. The number and severity of AEs.

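### The data source of the primary end point is contradictory: it is defined as nurse-assessed, but the analysis paragraph takes the parents' time first

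*Protocol article*

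**What the plan says.** Under Primary end point, the protocol article counts time from the first dose to "the start of the first 24-hour period without diarrhoea as assessed by the nurse on duty". The Methods part of the Abstract says the same: "the start of the first 24-hour period without diarrhoea as assessed by the on-duty nurse". The Discussion adds that the nurse measures duration in 12-hour intervals.

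Under Secondary end points, item 1 is the corresponding time "as recorded by parents or guardians in an hourly checklist". Two assessors therefore define two separate end points.

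Analysis and reporting presents a lognormal accelerated failure time model, chosen because it handles "right-censored or interval-censored outcome data that are required for analysing our primary end point". The next sentence begins "If parents or guardians cannot specify the exact time of cessation of diarrhoea, then the assessment by the nurse on duty" and concludes that this 12-hourly finding is used in its place, as an interval-censored value. The following paragraph says that the parent-assessed secondary end point "will be analysed in the same way as the primary end point".

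**The concern.** The assessor is part of the definition of this end point. It is also the only thing that separates the primary from secondary end point 1. The fallback sentence stands in the discussion of the primary model and reverses the order: the parents' time is used when there is one, and the nurse's when there is not.

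An analyst who follows the definition uses nurse intervals for every child. An analyst who follows the fallback sentence uses parent times wherever they exist. They analyse different data and can reach different primary estimates and p-values. If the choice stays open, it could be made after both results are known. Under the fallback rule, whether a child contributes an exact or an interval-censored value would also depend on the parents' ability to name a time. Where the parents' time is used for both end points, the secondary cannot corroborate the primary.

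**Working it through.** **The text, side by side**

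| Child | Primary, by its definition | Primary, by the fallback sentence | Secondary end point 1 |
|---|---|---|---|
| Parents give an exact time | nurse interval | parents' time | parents' time |
| Parents cannot give one | nurse interval | nurse interval | not stated, unless the fallback carries over |

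In the first row the definition and the analysis rule give different values, and the rule makes the primary equal to the secondary. The article does not say how many children fall in that row.

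**Does the conflict affect the sample size?** Inputs from Sample size and statistical considerations: SD of log10 duration 0.27, a 20% decrease, two-sided 5% level, 80% power.

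- Effect: |log10(0.8)| = 0.0969.
- Normal approximation: n = 2 × (1.960 + 0.842)² × 0.27² / 0.0969² ≈ 121.9, so 122 per group. The t-test version gives 122.8, so 123, which is the stated figure.
- Inflation: 123 × 1.22 = 150.06, so 150 per group, as stated.

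The calculation rests on the variability of hospital stay and does not use the assessor. It stands whichever source is chosen.

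**What does a 12-hour nurse grid cost against exact times?** With σ = 0.27 treated as known and cut points t_k = 0.5k days, let z_k = (log10 t_k − μ)/σ. The share of information on the mean that is kept is

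Σ [φ(z_{k+1}) − φ(z_k)]² / [Φ(z_{k+1}) − Φ(z_k)].

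Power is Φ(0.0969 / (0.27 × √(2/n)) − 1.96), with n multiplied by the share kept.

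| Centre of the distribution | Information kept | Power, n = 123 | Power, n = 150 |
|---|---|---|---|
| Exact times | 100% | 80.4% | 87.5% |
| Mean log10 = 0.61 (10^0.61 = 4.07 days) | 99.3% | 80.1% | 87.2% |
| Median 2 days (assumption) | 97.6% | 79.4% | 86.7% |

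The losses of information are 0.7% and 2.4%. The largest loss of power is 80.4 − 79.4 = 1.0 point at n = 123 (0.97 before rounding).

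The loss is not uniform over follow-up. Near 4.07 days, a 12-hour interval is about 0.5 / 4.07 / 2.303 = 0.053 log10 units wide. Its variance if uniform is 0.053²/12 ≈ 0.0002, or 0.3% of 0.27² = 0.0729. For a child who recovers between 12 and 24 hours the width is log10(2) = 0.301, and 0.301²/12 = 0.0076 is about 10% of 0.0729. The averaged figures in the table are therefore the better summary.

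**The case against.** The strongest defence is that the article names the nurse as assessor in three places (Abstract, Primary end point, Discussion), and that the mention of interval-censored data suits a 12-hourly nurse assessment. On this view the fallback sentence is a rule for secondary end point 1 that ended up in the wrong paragraph. Alternatively, the nurse, who collects the checklist every 12 hours, may establish the time by asking the parents. Either is possible, but nothing in the article says so, and the sentence as placed governs the primary. The defence explains how the conflict could have arisen without removing it.

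Three stronger inferences are tempting and are not supported:

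- A reader might infer that the trial will in fact test a variable other than its declared primary. The article shows two incompatible instructions and does not show which will be followed.
- A reader might infer that nearly all primary values would be parent-reported, because the checklist is hourly. An hourly form says nothing about how completely it is filled in, and the article gives no share.
- A reader might infer that the two analyses are meant to be identical, because the secondary "will be analysed in the same way as the primary end point". That phrase most naturally refers to the model. Only if it also carries the fallback across do the two analyses coincide for every child.

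It is also fair to say that the trial is double-blind, that nothing in the article shows either source to be biased by arm, and that the model accepts a mixture of exact and interval-censored values. Redefining the primary as parent-reported would reconcile the text too, but it would mean rewriting the Abstract, the end point definitions and the Discussion.

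**Conclusion.** The point holds as a contradiction over the data source of the primary end point. It is not left to an analysis plan, because the article states both the definition and the conflicting rule, and a plan would have to overrule one of them. The consequence is an ambiguous primary variable: the two readings differ for every child whose parents give an exact time, an unknown share.

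Timing precision is not a good reason to put the parents' time first. Using nurse intervals throughout loses about 0.7% of the information at the protocol's mean log10 duration and about 2.4% at an assumed 2-day median, under about 1 point of power. These figures take the log SD of 0.27 as known and assume a regular 12-hour grid. The value of 0.61 describes hospital stay. Time from first dose to cessation is probably shorter, since discharge can follow 24 hours after symptoms stop, and this is why the 2-day case is shown.

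**What to change.** Before recruitment, which Trial status says had not begun, state one source for the primary. To agree with the Abstract, Primary end point and Discussion:

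- **Primary.** Use nurse assessments for every child. Treat the time as interval-censored between the last nurse round with diarrhoea before the first qualifying 24-hour diarrhoea-free period and the first round of that period. If there is no earlier round, start the interval at the first dose. Ignore any later relapse, because the end point is the first such period.
- **Secondary end point 1.** Move the fallback sentence here. Alternatively, analyse this end point from parent data only and treat missing times as censored, which avoids the overlap that nurse intervals would bring in.
- **Wording.** Remove the fallback sentence from the primary paragraph, and say that the cross-reference to the primary analysis covers the model and not the data source.

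Both sources are already collected, so the change is one of wording. The price is the small loss of precision given above, and 123 per group before inflation and 300 in total remain as planned.

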### Study design

This study is a multicentre, randomised, double-blind, placebo-controlled trial designed to assess the effect of adjunctive probiotic (*L. acidophilus*) therapy in children admitted to the hospital with acute watery diarrhoea. Laboratory endpoints from admission until discharge will be recorded, and colonisation will be assessed in an outpatient follow-up visit with the first 50 subjects who agree to prolonged participation.

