### Randomisation and blinding

The study pharmacist will create a computer-generated block randomisation with blocks of varying size and stratification by participating centre. The probiotic and placebo sachets will be prepared in 5-day treatment packages plus vomit doses as described below. These will be labelled in advance and kept in a secure location. Participant numbers, which correspond to a package of sachets, will be assigned to each enrolled patient in strict numerical sequence. The treatment packages will be dispensed according to the participant number once a patient is enrolled into the trial. A chronological log of all enrolled patients will be maintained, and the next available sequential study code will be assigned to patients as they enrol.

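### Randomisation is stratified by centre, but centre is in neither the primary model nor the second-step covariates, so the primary test is mildly conservative if centres differ

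*Protocol article*

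**What the plan says.** Study design describes a multicentre trial: "This study is a multicentre, randomised, double-blind, placebo-controlled trial". Randomisation and blinding specifies "computer-generated block randomisation with blocks of varying size and stratification by participating centre". Treatment groups and duration of treatment sets allocation at 1:1.

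Analysis and reporting names the primary model as a "lognormal accelerated failure time regression model, which models the log-transformed outcome as depending linearly on covariates". It then fixes the covariate set as empty: "The primary analysis will not adjust for any covariates, but, in a second step, we will additionally explore the effect" of a list of covariates. The covariates for this exploratory second step, which also define the subgroups, are "duration of diarrhoea prior to enrolment, prior treatment with antibiotics and prior treatment with probiotics, age and diagnosed pathogen by culture or PCR". Centre is not among them, and no stratified analysis is mentioned. In the same section, the viral load comparison "will be adjusted for the participant’s baseline viral load to increase power".

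**The concern.** The analysis does not reflect a restriction that the design places on allocation. Blocking within centre keeps the arms nearly equal in every centre, so a centre with longer or shorter illness contributes almost nothing to the chance difference between arms. A model without centre still counts that variation as noise. Its interval is then wider than the design warrants, and its nominal 5% test rejects too rarely under the null.

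This is not a detail left for a later analysis plan, because the article states the unadjusted rule outright. What is at stake is calibration and some efficiency for the primary comparison. The treatment estimate on the log scale is not biased.

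**Working it through.** **Inputs from the article (Sample size and statistical considerations).** SD of log10 duration 0.27; target a 20% decrease, so delta = |log10(0.8)| = 0.0969; two-sided 5% level; 80% power; 123 per group, raised by 22% to 150.

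**Input not in the article.** rho, the share of log-duration variance that lies between centres. The number of trial centres is not given either. I assume rho = 0, 2, 5, 10 and 20%.

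**Step 1: reproduce the plan's figure.** Normal approximation: n = 2 × (1.960 + 0.842)² × 0.27² / 0.0969² ≈ 122 per arm. The exact two-sample t calculation gives power 79.7% at 122 and 80.06% at 123, so 123 is reproduced. 123 × 1.22 = 150.06, which gives the 150.

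**Step 2: standard errors with balance within centre.** Hold the total SD at 0.27 and let n be the number per arm.
- Reported by the unadjusted model: SE_rep = 0.27 × sqrt(2/n).
- True: SE_true = 0.27 × sqrt(1 − rho) × sqrt(2/n).
- Ratio: SE_rep / SE_true = 1 / sqrt(1 − rho).

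**Step 3: operating characteristics.**
- Type I error, unadjusted: 2 × [1 − Phi(1.96 / sqrt(1 − rho))].
- Power, unadjusted: 1 − Phi[(1.96 × SE_rep − delta) / SE_true].
- Power with centre in the model: 1 − Phi[1.96 − delta / SE_true].

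Example with rho = 10% and n = 150: SE_rep = 0.27 × sqrt(2/150) = 0.0312 and SE_true = 0.0312 × sqrt(0.9) = 0.0296. Type I error is 2 × [1 − Phi(2.066)] = 3.9%. Power is 88.7% unadjusted and 90.6% with centre.

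| Assumed rho | SE too large by | Type I error, unadjusted | Power at 150/arm, unadjusted | Power at 150/arm, with centre | Points given up |
|---|---|---|---|---|---|
| 0% | 0% | 5.0% | 87.5% | 87.5% | 0 |
| 2% | 1.0% | 4.8% | 87.7% | 88.1% | 0.4 |
| 5% | 2.6% | 4.4% | 88.1% | 89.1% | 1 |
| 10% | 5.4% | 3.9% | 88.7% | 90.6% | 2 |
| 20% | 11.8% | 2.8% | 90.0% | 93.5% | 3.5 |

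Unadjusted power rises slightly with rho because the total SD is held fixed: a larger between-centre share means a smaller true sampling error.

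**Step 4: check by simulation.** Three equal centres, 300 children, an uncensored linear model on the log scale, 40,000 replicates per setting.
- rho 5%: type I error 4.3% unadjusted, 5.0% with centre; power 88.2% and 89.1%.
- rho 10%: type I error 4.0% and 5.1%; power 88.4% and 90.3%.
- rho 20%: type I error 2.9% and 5.0%; power 89.7% and 93.3%.

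Formula and simulation agree. Neither models censoring, including the 12-hour interval censoring, and both assume balance within centre.

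**The case against.** A prespecified unadjusted primary analysis of a randomised trial is valid, and here any error is on the safe side. The centre share may well be small, since the study aims place the trial in one city and all children are treated under one national guideline. If centres do not differ, nothing is lost. All of this stands, and it keeps the point modest. It does not justify leaving out the stratification factor, which costs almost nothing to include.

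Three stronger readings are tempting, and the article does not support them.

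- **That the trial is underpowered as planned.** The SD of 0.27 comes from three hospitals and appears to be pooled, so it would already contain between-centre variation. The 123 per group reproduces for an unadjusted comparison. The loss is relative to a centre-adjusted analysis, not to the stated 80%.
- **That leaving out age and pre-enrolment duration is the same error.** Allocation was not stratified on these, so the unadjusted standard error is correctly calibrated with respect to them. The article proposes to explore their effect and does not claim that they determine duration. Eligibility also limits pre-enrolment illness to under 3 days, which may restrict what that covariate can explain. The viral load precedent carries over only in part, because that adjustment uses a baseline value of the outcome itself and time to cessation has none.
- **That adjustment would raise power from 80% to 84–88%.** That needs an assumed 10–20% of variance explained jointly by centre, age and pre-enrolment duration, evaluated at 123 per arm. The article supplies no such share and recruits 150 per arm, where the same assumption moves power from 87.5% to about 90.6–93.5%.

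**Conclusion.** The point holds as a mismatch between design and analysis, of modest size. With a between-centre share of 5–10%, the unadjusted standard error is 2.6–5.4% too large and the primary test runs at 4.4–3.9% instead of 5%. About 1 to 2 points of power are given up at 150 per arm. At a zero share nothing is lost, and even at 20% the loss is about 3.5 points.

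The direction follows from stratified allocation combined with an analysis that ignores the strata. The size rests wholly on the assumed share and on leaving censoring aside. The primary analysis remains valid, since its error is conservative.

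**What to change.** Include centre, as a fixed effect or as strata, in the primary lognormal AFT model and in the second-step and subgroup models. Report the unadjusted model as a sensitivity analysis. With a correctly specified linear predictor on the log scale, the treatment coefficient keeps its meaning as a ratio of durations, so the question asked does not change.

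The cost is one sentence and one parameter for each centre beyond the first. Centre is known from randomisation, and the Trial status section says that recruitment has not begun. Prespecifying age and pre-enrolment duration in the primary model is optional. It may gain some precision, by an amount the article gives no means to estimate, and it should not be presented as correcting an error.
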